### Tools and data collection

#### Quantitative survey tool development

There will be two survey tools: a household survey and an agriculture survey. Components of the household survey are summarized in Table 4. The survey includes 18 modules that will assess basic demographic data of the household such as household composition and education status, food insecurity, 24-h diet recall of the female caregiver and index child, health information of the index child, a standard household possessions questionnaire, information on WASH practices and associated costs, fuel-efficient stove use, economic or social support provisions, garden use, knowledge of health behaviors, and a pre- and post-intervention standard metric survey. The following components will also be part of the household survey procedures:

**Table 4 Tab4:** Program monitoring and assessment of sustainability

Measure (by treatment group)	Time point of measurement	Type of data collection
**Circle participation**		
Participation in meetings (based on ID confirmation of participants)	Monitoring through program (MEAL)	NIPP Booklet, in-home visit
# of meetings attended by participants per cluster	Monitoring through program (MEAL data)	NIPP Booklet, in-home visit
**BCC and counseling**		
Fabrication of handwashing facilities	Endline, 2- and 6-month follow-up, sustainability	Quantitative
Fabrication of simple latrines	Endline, 2- and 6-month follow-up, sustainability	Quantitative
Fabrication of fuel-efficient stoves	Endline, 2- and 6-month follow-up, sustainability	Quantitative
Continued use of handwashing facilities	2- and 6-month follow-up and sustainability	Quantitative
Continued use of latrines	2- and 6-month follow-up and sustainability	Quantitative
Continued use of fuel-efficient stoves	2- and 6-month follow-up and sustainability	Quantitative
Infants/young children achieving minimum acceptable diet	Endline, 2- and 6-month follow-up, sustainability	Quantitative
Newborns being exclusively breast fed	Endline, 2- and 6-month follow-up, sustainability	Quantitative
Newborns receiving complementary foods at 6 months	Endline, 2- and 6-month follow-up, sustainability	Quantitative
**Micro-gardening**		
Planted micro-garden	Endline	Quantitative
Continued maintenance of a micro-garden	2- and 6-month follow-up and sustainability	Quantitative
Using produce for household consumption	Endline, 2- and 6-month follow-up, sustainability	Quantitative
Selling produce from micro-garden	Endline, 2- and 6-month follow-up, sustainability	Quantitative
**Water quality**		
Reported knowledge of water quality assessment	Baseline, endline, 2- and 6-month follow-up sustainability	Quantitative
Reported purchase of water tests	Endline, 2- and 6-month follow-up, sustainability	Quantitative
Reported use of water tests	Endline, 2- and 6-month follow-up, sustainability	Quantitative
**Assessment of moisture**		
Reported knowledge of moisture assessment	Baseline, endline, and sustainability	
Reported purchase of hygrometers	Endline, 2- and 6-month follow-up, sustainability	Quantitative
Reported use of hygrometers	Endline, 2- and 6-month follow-up, sustainability	Quantitative
**Assessment of storage**		
Reported knowledge of improved storage	Baseline, endline, and sustainability	Quantitative
Reported purchase of hermetic storage bags	Endline, 2- and 6-month follow-up, sustainability	Quantitative
Reported use of hermetic storage bags	Endline, 2- and 6-month follow-up, sustainability	Quantitative
**Use of improved varieties and fertilizer**		
Reported purchase of improved maize varieties	Baseline, endline, and sustainability	Quantitative
Reported planting of improved maize varieties	Baseline, endline, and sustainability	Quantitative
Reported knowledge of vendors for improved varieties	Baseline, endline, and sustainability	Quantitative
# of interactions with vendors	Baseline, endline, and sustainability	Quantitative
Reported knowledge of fertilizer availability	Baseline, endline, and sustainability	Quantitative
Reported use of fertilizer	Baseline, endline, and sustainability	Quantitative
Reported use of improved seed varieties for the planting season after the intervention	Endline, 2- and 6-month follow-up, and sustainability	Quantitative

#### Anthropometry data collection

Children’s nutritional health status will be measured using standard anthropometric measures: mid-upper arm circumference (MUAC), weight, and height/length and presence of edema. Three measures of each indicator will be taken at the time points specified in Table 2. Female caregivers will also be assessed via anthropometry, specifically weight and MUAC. The enumerator training will be composed of a maximum 2-day training on anthropometry. At the end of the training, enumerators will be tested on the tool and their anthropometry skills. For the latter, we will use the Standardized Monitoring and Assessment of Relief and Transitions (SMART) approach where each enumerator will measure three to five children five times each. Given the importance of collecting accurate anthropometry data, in the field, enumerators will collect three measurements on height and weight for each child.

#### Blood or urine collection and aflatoxin assessment

Aflatoxin levels for the subsample of females and household’s eligible child/children or female caregivers will be assessed using finger-prick samples and/or 10 ml urine using field-friendly point-of-care diagnostic kits. These point-of-care diagnostics will be collected by trained enumerators or phlebotomists in collaboration with local government health systems and taken to a central makeshift lab suitable for diagnostic testing in field settings like Agogo. This method may also be used to test for aflatoxin contamination in the maize samples themselves along with the reference method.

#### Water sample collection for assessing *E. coli* and total coliforms

Microbiological water samples taken from the home and community will be processed within 6 h of sample collection using a membrane filtration method containing m-ColiBlue24 media (Hach Company, Loveland, CO). This method allows for the simultaneous analysis of *E. coli* and total coliforms. We will request each household to provide a 250-ml water sample from the storage container that is used for drinking purposes. At the community level, we will identify the common water sources and request the participants to provide a sample of 250 ml from each common water source. If households within a circle are using different water sources, we will collect a sample from each of the water sources used by the circle participants. For both household and community assessments, the sample will be transferred from a storage container to a sterile plastic bottle, placed into a cooler, and transported back to a makeshift lab where the water will be analyzed for *E. coli* and total coliforms. As we will only need 360 household samples per data collection (baseline, endline, sustainability), we will randomly select these households in advance in such a way that we are collecting 6 samples per every cluster (60 clusters × 6 samples = 360 samples). The same 360 households will be sampled at each time point. The community samples will be collected from every cluster.

At the lab, all water samples will undergo the following process: dilution with sterile buffered water, vacuum-filtered aseptically through 45-μm filters (EMD Millipore, Billerica, MA), placed in plastic Petri dishes with media-soaked pads, and incubated for 24 h at 35 °C. Two dilution volumes will be processed per water sample. As a standard quality control process, 10% of samples will be duplicated and 5% of samples will be blank/control. After incubation, colonies of bacteria will be counted, and concentrations calculated using the geometric mean of plate counts within a countable range (1–250 colonies). Plates with counts < 1 will be assigned 0.5 and > 250 were assigned 250.

As summarized in Table 4, the agriculture survey will be composed of 6 modules that capture information on crop diversity, agriculture inputs, crop yields and production, agriculture practices, and knowledge of GAP. In addition to capturing information through the survey, there will also be samples taken of harvested maize using the following method.

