Community-based interventions to decrease contamination of communities’ water sources include building improved sources (e.g., boreholes) and encouraging community members to gather water from these improved sources [12]. However, household preferences for unimproved water sources like rivers whether out of convenience (closer to the home) or habit (gathering point for community members) may lead to higher rates of microbial infections [12–14]. Even when households collect water from boreholes, microbial contamination is likely because of transportation, storage practices, and household water management habits [15, 16]. Water chain management from source to point of use, community management of human and animal fecal matter, and individual household hygiene practices all impact contamination levels of households’ drinking water and are linked to children’s nutritional outcomes including increasing the risk of relapse into acute malnutrition after nutritional rehabilitation [13, 17, 18]. A sub-study of the Uganda birth cohort reported the potential for point of use (i.e., household-based) water quality improvement interventions in decreasing *E. coli* contamination of household drinking water, thus decreasing the severity of environmental enteric dysfunction (EED: an inflammatory process linked to poor health and hygiene) and improving growth in infants aged 12–16 months [19].

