### Intervention preparation

#### NIPP and NIPP+ intervention training/session modules

Through the 12-week intervention period, NIPP volunteers will conduct sessions that will cover the following elements to the circle participants:
Promotion of food hygiene practices;How to keep the water source safe by identifying the small doable actions that will be used as a metric of assessment such as:
Using different containers for transportation and storage of household potable water;Regular cleaning of storage and transportation water containers;Handwashing and use of tippy taps to conserve water;Separate animals from humans within the household to reduce fecal contamination of water;Use of simple water purification methods (e.g., boiling, solar disinfection, etc.) (NIPP+ only);Demonstrate how simple water quality kits can identify contamination (NIPP+ only); andDemonstrate simple methods (at the household and community levels) to support improving the quality of water (Hamoudi, 2012) (NIPP+ only).

To reinforce impact and empower the women and men in the NIPP circles, we will encourage them to maintain a record of their results on forms adapted for the general literacy levels of the target populations. All materials will be tested and contextualized to the local situation and translated into Acholi.

Agricultural demonstration plots will be planted and used to train the NIPP+ volunteers on GAP. The harvest from the demonstration plots will be bagged in both hermetic and non-hermetic storage bags to use for demonstration at the NIPP+ volunteer training. We anticipate providing hermetic bags, seed packs, and fertilizer samples to the NIPP+ volunteers who will demonstrate the use of these inputs within their own circles. Volunteers will be encouraged to store their maize from the harvest of the demonstration plots in hermetic bags to show the circle participants the benefits of using the bag.

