**Primary outcome measure**			
Nutrition	Women’s dietary diversity Infant and young child dietary diversity	Baseline, endline, 2- and 6-month follow-up, and sustainability	Quantitative
Water quality	*E. coli* (colonies/100 ml) at household and community water source	Baseline, endline, sustainability	Quantitative
	*E. coli* at household and community water		
Food safety	Aflatoxin levels in grain samples Aflatoxin levels (urinary and finger prick)	Endline, sustainability	Quantitative
Food security	Months of adequate household food provisioning, food security access scale	Baseline, endline, and sustainability	Quantitative

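### The primary community-source E. coli outcome can include container contamination that differs by arm, because the sampling text routes the source sample through a storage container

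*Protocol article*

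**What the plan says.** Table 3 of the protocol article lists E. coli as the primary water-quality measure at baseline, endline and sustainability; the entry reads in part "colonies/100 ml) at household and community water source". Household and community source are thus two sampling points.

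The section on water sample collection describes the sampling in four statements:

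- Household: "We will request each household to provide a 250-ml water sample from the storage container that is used for drinking purposes".
- Community: the team identifies the common sources and will "request the participants to provide a sample of 250 ml from each common water source".
- Where a circle uses several sources: "we will collect a sample from each of the water sources used by the circle participants".
- Transfer: "For both household and community assessments, the sample will be transferred from a storage container to a sterile plastic bottle".

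The section does not describe filling a sterile bottle directly at a source, and it does not say whose container is used for the community sample. Community samples are taken in every cluster; household samples are 6 per cluster, 360 per round.

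The list of session modules includes "Regular cleaning of storage and transportation water containers" and the use of different containers for transport and storage. Neither item is marked as NIPP+ only. The control group receives no intervention.

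**The concern.** A source measurement should not depend on the vessel that carried the water. The article's own Introduction says that even for borehole water "microbial contamination is likely because of transportation, storage practices, and household water management habits". If the community sample passes through a container before the sterile bottle, that contamination enters a primary outcome.

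The containers are also a target of the programme in two of the three arms. Cleaner vessels in NIPP and NIPP+ could make an unchanged source look cleaner there than in control. The participants asked to supply the water know their arm, because the article says allocation cannot be concealed from them. At stake are a possible report of improved community water where only vessels changed, and a blurred comparison between source and point of use, which the Introduction treats as a chain.

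**Working it through.** **Which statement governs the community sample?** The participant-request sentence and the sentence in which the team collects leave open who draws the water. The transfer sentence does not leave open the vessel: it names community samples explicitly and gives them the same step as household samples. A team that follows the text may therefore use a container, possibly a participant's.

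**What is then measured?** Write the expected community reading in arm a at round t as

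Y(a,t) = S(a,t) + C(a,t),

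where S is the source and C is the container contribution. Against control (arm 0), the difference-in-difference between baseline and a later round is

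[change in S in arm a − change in S in arm 0] + [change in C in arm a − change in C in arm 0].

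The first bracket is the target. The second is bias. A container error that is constant over time cancels. One that falls in the active arms because containers are cleaned after training does not cancel. Intention-to-treat analysis and adjustment for household and child characteristics do not touch it either. In the endline-to-sustainability contrast, only a further change in C enters.

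**Which contrasts are exposed?** The container messages go to both active arms, so C is expected to move in NIPP and in NIPP+ but not in control. NIPP+ also has purification methods and jerry cans for its volunteers, so NIPP+ versus NIPP is less exposed but not immune.

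**How large?** No figure in the article fixes the shift. To show how sensitive the comparison is, assume:

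- 20 clusters per arm (from the article);
- k independent source readings per cluster (assumed, since the number of sources is not given);
- true source difference 0;
- normal readings with equal variance;
- one pairwise two-sided test at 0.05.

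With n = 20k readings per arm and a container shift of b SD between arms, the test statistic is noncentral t with df = 2n − 2 and noncentrality b × √(n/2). For k = 1, df = 38 and √(20/2) = 3.162, so b = 0.3 gives 0.949. For k = 2, df = 78 and √(40/2) = 4.472, so b = 0.3 gives 1.342.

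| Container shift b (SD) | P(false source effect), k = 1 | k = 2 |
|---|---|---|
| 0.1 | 0.061 | 0.073 |
| 0.2 | 0.095 | 0.143 |
| 0.3 | 0.152 | 0.263 |
| 0.5 | 0.338 | 0.598 |
| 0.67 | 0.542 | 0.841 |

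The last row equals the E. coli effect size in Table 2 (0.67 × 45.14 = 30.2 colonies). Bacterial counts are skewed and the plate counts are capped, so the table is a rough guide, not an estimate.

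**What is untouched?** Household samples are meant to come from the drinking-water container, so for them the transfer sentence is correct. The planned 60 × 6 = 360 household samples, and the sample size, are unaffected.

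**The case against.** The strongest reply is that the text is loose, not wrong. The water is said to come from each common source. One sentence has the team collecting it, and the data collection section says enumerators are trained in water collection. The container is unspecified: it could be a clean collection vessel, or household wording carried over. A condensed article may leave vessel-level instructions to a field manual. The Introduction's remark concerns transport, storage and household management, not a fresh draw handed over for testing.

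Much of this stands, and it limits the point. A reader might infer that the outcome measures containers instead of the source. It does not: on the least favourable reading it measures both. A reader might also infer that the source versus point-of-use contrast is lost. It is blurred, because storage time and household handling still separate the two samples.

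A reader might also size the bias by setting the source count to zero, attributing the whole Table 2 mean of 31.56 to containers and letting training remove 25%, 50% or 75% of it: 7.9, 15.8 or 23.7 colonies. The article supports none of those assumptions, and Table 2 does not say at which point its mean was measured.

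The reply does not remove the transfer sentence. It is not an omission left to a manual; it states a procedure for community samples that lets container contamination in.

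**Conclusion.** The point holds in a limited form. As written, the sampling text does not keep the primary community-source E. coli outcome free of container contamination. Because only the active arms are taught container hygiene, the error can differ by arm after baseline, in the direction that favours NIPP and NIPP+ over control.

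This rests on two assumptions: that the transfer sentence is followed, and that the container is one whose cleanliness the programme can change. The documents settle neither, so this is a risk built into the procedure and not a demonstrated bias. Its size is unknown. Under the stated assumptions with one reading per cluster, the false-positive probability runs from 0.06 at a shift of 0.1 SD to 0.34 at 0.5 SD.

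**What to change.** Reconcile the sentences in the water-sampling section so that:

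- trained enumerators fill the sterile bottle directly at each common source, with no intermediate container;
- the procedure is the same in all three arms;
- the storage-container transfer applies to household samples only.

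Recruitment began in March 2021, endline falls 4 months after baseline and the article appeared in April 2022, so early rounds may already have been collected. Establish how each was taken. Label any round that used containers as source-plus-container water, and do not compare it with a directly sampled round as a change in source quality. Compare arms within a round instead. In a directly sampled round that comparison concerns the source; in a container round it remains source-plus-container and should be reported as such.

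The cost is a short text change and enumerator walking time; teams already sample in every cluster. If earlier rounds used containers, this one outcome also loses its like-for-like baseline, and with it the baseline difference-in-difference. No change to the sample size follows.

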#### Method for sampling aflatoxin assessment in grain

The study team will collect grain samples from all households (*n* = 900). These will be analyzed for aflatoxins by International Maize and Wheat Improvement Centre (CIMMYT) at a makeshift lab established in Agago. Moisture levels in the staple crops will also be assessed on-site using existing moisture meters (from CIMMYT) that will allow the research team to corroborate the findings from the household monitoring using the hygrometers. For the aflatoxin assessment, grain will be collected in the home. If maize is stored in cobs, one cob of maize will be randomly selected from the home store at each assessment point The cobs will be hand shelled and thoroughly mixed to form a composite sample per household then dried on plastic mats to 14% moisture content. A 1-kg sample will be taken per household and transported to the laboratory for aflatoxin extraction and analysis. If the households have shelled the maize, samples will be taken from the storage bags using sampling spears, taking five samples per bag, thoroughly mixing the sample, and take a subsample of about 1 kg. Samples will be stored in a deep freezer (− 20 °C) until processing. For aflatoxin extraction, 50 g of maize flour will be transferred to a 250-ml flask, and 100 ml of 70% methanol (v/v 70 ml absolute methanol in 30 ml distilled water containing 0.5% w/v potassium chloride) will be added. The samples will be shaken for approximately 30 min at 300 rpm. The extract will be filtered through filter paper and diluted 1:10 in phosphate-buffered saline containing 500 μl/l Tween-20 (PBS–Tween). The extracts from the samples will be analyzed with an indirect competitive enzyme-linked immunosorbent assay (ELISA). Alternative low-cost options such as strip tests will also be explored.

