*Hygrometers*^3^: standard devices that measure humidity and temperature of produce stored in home settings developed through a collaboration between Purdue University, CIMMYT, KALRO, and USAID. These devices measure the relative humidity in the air. When placed in a hermetic bag with grain, the reading will inform the farmer if the air inside (and the grain by proxy) is too wet (i.e., if greater than 65% humidity) or at an acceptable level to prevent mold growth. Using hygrometers ensures that maize is properly dried before storage. To introduce the hygrometers to participants, a practical session in which grain samples that have been exposed to different levels of moisture are placed in a storage bag and the hygrometer is used to measure the humidity. This will be integrated into the module detailing proper drying techniques after shelling, using a tarp.*Hermetic bags:* portable and reusable 50-kg storage bags made from thick polyethylene that restrict gas exchanges such that the oxygen in the bag is replaced by carbon dioxide through natural processes in the maize. This process kills insects and stops fungal growth and the production of aflatoxins in the stored grain. At least one bag will be provided for free to every household, and more will also be made available through market vendors.*Improved seed varieties:* maize varieties tolerant to different stresses (drought, low soil fertility, and disease) have been developed and tested widely in partnership with the National Agricultural Research Organization (NARO) in different parts of Uganda, including northern Uganda. These new stress-tolerant maize varieties are high yielding and are important in improving maize productivity at the farm level through enhanced yields and resilience to various abiotic and biotic stresses commonly encountered by farmers. They are produced by local seed companies and distributed through private-sector agro-dealers.*Training in good agronomic practices (GAP):* Integrated soil fertility management (ISFM) practices will be implemented to increase crop productivity in a profitable and environmentally friendly way. These practices include (1) the combined use of organic manure and mineral fertilizers and (2) dual-purpose legume-cereal rotations and inter-cropping. Inter-cropping and crop rotations help in preventing pests and diseases to spread throughout the field, increase soil fertility, especially in the case of legumes, help in controlling weeds, and will be adapted to the local conditions/farming context. Farmers will be trained on improved maize varieties and good agronomic practices during on-farm demonstrations.

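### The maize-sampling rule asks for one cob but also a composite and 1 kg, and it samples cob-stored and shelled maize unequally for a primary outcome

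*Protocol article*

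**What the plan says.** All of the sampling text is in the protocol article, under the heading on sampling grain for aflatoxin.

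- **Cob-stored maize, selection:** "If maize is stored in cobs, one cob of maize will be randomly selected from the home store at each assessment point".
- **Cob-stored maize, handling:** "The cobs will be hand shelled and thoroughly mixed to form a composite sample per household then dried on plastic mats to 14% moisture content".
- **Mass:** "A 1-kg sample will be taken per household and transported to the laboratory for aflatoxin extraction and analysis".
- **Shelled maize:** "samples will be taken from the storage bags using sampling spears, taking five samples per bag, thoroughly mixing the sample", from which a subsample of about 1 kg is kept. No drying step is stated for this branch.

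The rule is the same in all three arms and branches on how the household stores its maize. Under Study groups, only NIPP+ supplies hermetic bags ("At least one bag will be provided for free to every household, and more will also be made available through market vendors"), teaches drying after shelling, and places hygrometers in bagged grain. Standard NIPP lists grain storage as a discussion topic, and the control arm receives nothing.

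Table 3 lists aflatoxin in grain as a primary outcome at endline and sustainability only. The Data collection section likewise places both grain collections after the intervention. The statistical methods section plans ordinary least squares, Poisson or negative binomial regression for continuous outcomes, chosen by distribution, and logit for binary ones.

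**The concern.** There are two linked problems.

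1. **The cob rule cannot be carried out as written.** A single cob is not a composite of cobs and will not plausibly yield 1 kg. Field teams must depart from one sentence or another, and the article does not say which governs. Different teams may resolve it differently.
2. **The two storage forms are sampled with unequal precision.** A mixed sample of five spear draws per bag averages over many kernels from different places in the store. One cob does not. If contamination varies from cob to cob, a one-cob value is a far noisier measure of what the household holds. Drying is also stated for one form only.

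The first cost is power for a primary outcome. Aflatoxin is also the row of Table 2 that sets the trial at about 900 households. The second is comparability. The NIPP+ inputs all concern shelled grain, so the share of households sampled under each rule may differ by arm. With no baseline grain sample, a baseline difference-in-difference cannot remove a resulting artefact.

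**Working it through.** **Inputs from the article (Table 2 and the sample size section):** mean 20, SD 43.6, effect size 0.34, ICC 0.05, power 0.80, significance level 0.05 (taken as two-sided), 17 clusters of 15 per arm, 20% for attrition.

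**Assumptions, because the article gives no figure:** 0.1 to 0.3 kg of kernels per cob; coefficient of variation (CV) of a one-cob value around the household mean of 1 to 3; CV of a bag composite 0.2; the shares of households storing shelled maize.

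**1. The plan's own figure.** n per arm without clustering = 2 × ((1.96 + 0.84)/0.34)² ≈ 136. The design effect is 1 + 14 × 0.05 = 1.7, giving about 231, or 15.4 clusters of 15. A cluster-level t test has power 0.789 with 16 clusters and 0.815 with 17, so 17 is reproduced. Then 17 × 15 = 255 and 255 × 1.2 = 306, as in Table 2.

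**2. Mass.** 1 kg ÷ 0.3 kg = 3.3, so 4 cobs; 1 kg ÷ 0.1 kg = 10 cobs. One cob falls short throughout the assumed range.

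**3. Power if one cob is used.** Let a share q of households in each arm be cob-sampled.

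- Added variance = q × CV² × (20² + 43.6²) = q × CV² × 2301. The base variance is 43.6² = 1901.
- Diluted effect d′ = 0.34 × √(1901/(1901 + added)). The ICC shrinks by the same variance ratio.
- Power ≈ Φ(d′ × √(n_eff/2) − 1.96), with n_eff = 255/(1 + 14 × ICC′).

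With no added noise: n_eff = 150 and 0.34 × √75 = 2.94, so power is 0.84.

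With q = 0.5 and CV = 2: added = 4602; d′ = 0.34 × √(1901/6503) = 0.184; ICC′ = 0.0146; n_eff = 212; power 0.47.

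For a composite of k independent cobs, CV² is divided by k. With k = 10 and CV = 2: added = 460; d′ = 0.305; ICC′ = 0.040; n_eff = 163; power 0.79.

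| q = 0.5 | CV 1 | CV 2 | CV 3 |
|---|---|---|---|
| One cob | 0.72 | 0.47 | 0.30 |
| Ten-cob composite | 0.82 | 0.79 | 0.73 |

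**4. Arithmetic means, no true effect.** I simulated 17 clusters of 15 per arm with lognormal household values (mean 20, SD 43.6). The difference in means stayed near zero, with type I error of 4% to 7%, even with shelled shares of 20% v 90%. A second model, with 10% of cobs at 200 and the rest at 0, was fitted by OLS, Poisson and negative binomial regression with cluster-robust errors. With cob shares of 70% v 30% the OLS difference was about −0.04 and the ratios about 1.005. With 100% v 0% the ratios were about 1.01. Rejection rates were between about 5% and 9%, so the point estimates are essentially unbiased.

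**5. Log scale, no true effect.** With lognormal sampling error, a one-cob value lies on average ½ ln(1 + CV²) below the log of the household mean, and a bag composite ½ ln(1.04) below. The spurious log ratio is the difference in shelled share times the gap between these. For 30% v 70% and CV 3: 0.4 × ½ × (ln 10 − ln 1.04) = 0.453, a geometric-mean ratio of 1.57. The simulation gave:

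| Shelled share, control v NIPP+ | Geometric-mean ratio (CV 1 to 3) | Type I error, log scale |
|---|---|---|
| 50% v 50% | 1.00 | 4% to 5% |
| 50% v 70% | 1.06 to 1.25 | 6% to 23% |
| 30% v 70% | 1.14 to 1.57 | 12% to 67% |
| 20% v 90% | 1.25 to 2.19 | 27% to 99% |

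For the share of households above 20, type I error reached 34% in the worst case. In this model NIPP+ reads higher, so a real benefit could be hidden.

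**The case against.** The strongest reply is that this is a wording slip. If the composite and 1-kg sentences govern, cob-storing households also give a multi-cob sample and most of the precision gap disappears. That is fair: the article does not establish a one-cob design, and the power figures apply only if the selection sentence is followed literally. But the procedure is stated, and stated inconsistently, so this is not detail left to a fuller document.

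A reader might go further and infer that aflatoxin is measured differently in each arm, so that the arm contrast is biased and control looks cleaner. The documents do not support that, for three reasons.

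- The planned models target arithmetic means. Poisson and negative binomial regression use a log link, not a logged outcome, so their arm coefficient is a log ratio of arithmetic means, which one-cob sampling leaves about unchanged. No log transformation or aflatoxin threshold is named.
- No share of households storing on the cob is given for any arm. The shelled branch covers storage bags in general, so a control household using ordinary sacks is sampled exactly as a NIPP+ household is. Free hermetic bags may change the kind of bag rather than move maize off the cob.
- Table 2 gives no unit or matrix for its mean of 20, and its footnote refers to aflatoxin in mothers, so calculations using that row are illustrations for grain.

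Reported hermetic-bag use is collected (Table 4), but the article does not tie storage form to each grain sample.

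**Conclusion.** The point holds as an internal contradiction and an unequal sampling rule for a primary outcome. One cob cannot plausibly yield the composite and the 1 kg the same paragraph requires, while shelled maize gets five draws per bag and no stated drying step.

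The main consequence, if one cob is taken, is lost power. Under the stated assumptions, with half of households cob-sampled, power falls from 0.84 to between 0.72 and 0.30. The real size is unknown, because it rests on a cob-to-cob variance and storage shares that the article does not give.

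A difference between arms in the mix of storage forms is a plausible inference from the NIPP+ inputs, not a stated fact. It would leave the planned comparisons of arithmetic means about unbiased. It would distort a log-scale, median or threshold analysis if one were chosen, and the absence of baseline grain means that could not be corrected afterwards. The claim of a biased primary comparison should not be made.

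**What to change.** 1. Replace the single cob with a fixed number of cobs drawn at random from different positions in the store, enough to give the 1-kg composite (about 4 to 10 on the assumed kernel weights; ten would cover the range) and comparable in increments to the bag rule.
2. State one drying step and apply it to both storage forms.
3. Record with each sample the storage form and the number of cobs or bags drawn from. For any collection already done, document what was actually taken.
4. Keep the comparison of arithmetic means as the main analysis of grain aflatoxin. Report results by storage form as descriptive only: storage form arises after randomisation and may be changed by NIPP+, so an arm contrast within it is open to selection bias and removes part of the storage pathway.

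**Cost:** a few more minutes and slightly more grain per cob-storing household. The 1-kg sample per household is already planned, so no assays are added.
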